## Abstract

**Background:**

Intermediate-risk prostate cancer (PCa) is currently managed with radical whole-gland therapies, such as radical prostatectomy (RP) or radiotherapy (RT). While effective, these treatments can significantly impact quality of life (QoL), particularly in relation to urinary incontinence and erectile dysfunction. Focal therapy poses a promising alternative for whole-gland treatment in this specific patient population; however, current evidence has primarily been limited to phase I and II studies. Robust prospective evidence is needed to determine whether focal therapy can be considered a safe alternative for management of intermediate-risk PCa. The objective of this randomised controlled trial (RCT) is to evaluate the oncological effectiveness, QoL and cost-effectiveness of focal therapy compared with radical treatment as standard of care.

**Methods:**

This ENFORCE focal study is designed as a multicentre RCT with six participating centres that perform focal therapy in the Netherlands. Patients are included after receiving informed consent and are thereafter 1:1 randomised between focal therapy, consisting of high-intensity focused ultrasound, irreversible electroporation or transurethral ultrasound ablation and radical treatment, consisting of RT or RP. A total of 356 patients will be enrolled. This study has two co-primary endpoints, oncological effectiveness at 36 months (non-inferiority) and QoL at 12 months (superiority) both of which must be met to demonstrate overall trial success. Follow-up will be at least 3 years, with a maximum of 5 years to gain information regarding long-term outcomes. The set follow-up visits are 6 weeks, 3 months, 6 months, 12 months and yearly thereafter. At the follow-up visits, clinical data will be collected, and questionnaires regarding QoL and costs will be administered. Furthermore, at 9 months and 18 months, prostate-specific antigen will be monitored in alignment with European guidelines on follow-up after RP and RT. Primary analyses will be conducted using intention-to-treat analyses.

**Ethics and dissemination:**

Ethical approval has been obtained from the Medical Research Ethical Committee Oost-Nederland (NL83913.091.23, primary approval in December 2023; last approved version 10 July 2025). The results will be submitted for publication in peer-reviewed medical journals, and data will be accessible.

**Trial registration:**

NCT06223295.

STRENGTHS AND LIMITATIONS OF THIS STUDYComparison between the groups of therapies, rather than a one-to-one comparison of individual therapies.No differences have been observed between different focal therapies, but these techniques have not been directly compared within a single study.A difference in follow-up protocols between the treatment arms.Quality of life will be assessed using patient-reported questionnaires, which may be subject to bias.

## Introduction

 In current clinical practice, intermediate-risk prostate cancer (PCa) is typically managed using radical whole-gland treatment, such as robot-assisted radical prostatectomy (RP) or a form of radiotherapy (RT). These treatments are known to be associated with complications, mainly consisting of incontinence and erectile dysfunction, affecting 21% and 70% of patients with RP, respectively.^1^ For patients with RT, urinary complaints, such as frequency, urgency, urethral stricture or incontinence, are observed in up to 27% of the patients, erectile dysfunction in up to 29% and gastrointestinal toxicity in up to 11%.^2^ These side-effects from RT and RP can substantially impact quality of life (QoL) of patients.

PCa is a heterogenous disease, with a risk classification ranging from low to high risk, requiring different treatment approaches. While radical treatment for high-risk disease results in favourable oncological outcomes,^3^ evidence shows that active surveillance (AS) is a safe approach for low-risk PCa without increasing the risk of unfavourable outcomes.^4^ AS is close monitoring, using prostate-specific antigen (PSA), MRI and biopsies, of PCa without immediate treatment. Although intermediate-risk PCa often requires treatment, it is debatable if patients with less aggressive tumours than high-risk patients also require a radical whole-gland treatment.^5^

Patients are becoming more assertive, increasingly informed about available treatment options and more actively involved in making decisions about their healthcare, the so-called shared decision making. Furthermore, patients seem to be willing to sacrifice some survival to improve their QoL.^6 7^ In this context, focal therapy, which treats only the tumour-bearing portion of the prostate, may be a valuable treatment option for patients with intermediate-risk PCa. Over the past decade, research into focal therapy for PCa has explored different energy sources, such as high-intensity focused ultrasound (HIFU), irreversible electroporation (IRE), cryoablation, focal laser ablation (FLA) and photodynamic therapy (PDT).^7^ These different types of energy transmission all seem to be feasible focal treatments.^8^ All these focal therapies are aimed at patients with low- and intermediate-risk PCa. The concept of focal therapy is founded on the premise of preserving QoL while maintaining oncological control. The rationale for this concept is based on the index lesion theory.^9^ The index lesion theory holds that PCa is often multi-focal, with one index lesion being the main determining factor of tumour behaviour, aggressiveness and disease progression. Other lesions are often clinically insignificant and contribute not at all or in a much smaller portion to disease progression over a 10–20-year period.^10^ Focal therapy targets the ablation of the MRI-visible, biopsy-confirmed index lesion along with an appropriate safety margin, aiming to achieve oncological outcomes comparable to those of radical treatments in patients with low- or intermediate-risk PCa.^11 12^ Furthermore, treating only part of the gland is thought to preserve most of the function, potentially leading to a better QoL compared with whole-gland treatment. To achieve this precise treatment, it is necessary to use peri-operative image guidance, typically through MRI or ultrasound (US). Focal therapy has the potential to delay or even eliminate the need for radical treatment by slowing disease progression. Currently, most patients will undergo an AS regime after focal therapy, including PSA measures, MRI and possibly prostate biopsy. In the event of recurrence or the appearance of a new lesion, patients can still undergo radical treatment or receive additional focal therapy.^13^

Despite current research into focal therapies for PCa,^7^ there is still a lack of high-quality, Idea, Development, Exploration, Assessment, Long-term (IDEAL) stage 3 evidence, as most existing studies are limited to IDEAL stages 1, 2a and 2b. These previous studies often have considerable heterogeneity in study design, patient populations and ablative protocols, making it difficult to compare the efficacy of different ablation modalities.^8 14^ Furthermore, current evidence on the cost-effectiveness of focal ablation techniques is insufficient to inform guidance regarding their routine clinical use.^15^ This underlines the need for a multicentre randomised controlled trial (RCT) to determine the role of focal therapies in the treatment of intermediate-risk PCa. Currently, several RCTs are underway, often comparing one focal therapy modality with one type of standard of care, for example, RP, such as the CAPTAIN trial (trial registration: NCT05027477), the PRIS trial^16^ and the PART trial (trial registration: ISRCTN17249875). In contrast, our ENFORCE focal study adopts a broader approach by comparing multiple focal therapy modalities, consisting of HIFU, transurethral ultrasound ablation (TULSA) and IRE, against various radical standard-of-care treatments. This design distinguishes ENFORCE focal from other RCTs, producing more generalisable results helping real-world decision making in daily practice.

Our RCT aims to study the (cost-)effectiveness of focal therapy compared with radical whole-gland treatment in men with intermediate, unilateral PCa in terms of oncological effectiveness and QoL.

## Methods

### Design

ENFORCE focal is a pragmatic multicentre, RCT comparing the (cost-)effectiveness of focal therapy to radical whole-gland treatment, that is, RP or RT, in patients with intermediate-risk PCa. Patient recruitment will be performed in outbound patient clinics in six Dutch centres and their networks. Each participating centre performs a focal ablation technique and radial whole-gland treatment. Focal therapies applied in the study are TULSA, HIFU and IRE; each centre performs one of the focal therapies. Radical treatment will be performed as per normal routing. This means that RP will be performed by the urologist in the participating centres or in their collaborative network, and patients choosing RT will be referred to RT centres. Within the trial, one of the participating centres collaborates with a dedicated HIFU clinic where the focal treatment is carried out. Follow-up will be at least 3 years, with a maximum of 5 years to gain information regarding long-term outcomes. The set follow-up visits are 6 weeks, 3 months, 6 months, 12 months and yearly thereafter. At the follow-up visits clinical data will be collected, and questionnaires regarding QoL and costs will be administered. Furthermore, at 9 months and 18 months PSA will be monitored in both groups in alignment with European guidelines on follow-up after RP and RT. For the focal therapy arm, at 12 months, an MRI and prostate biopsies will be performed. In the years thereafter, a prostate MRI will be performed yearly with additional biopsies on indication, such as rising PSA levels over time, suspicious MR findings in the treated zone or newly identified lesions outside the treated area.

### Outcome measures

#### Primary endpoints

The co-primary outcomes are oncological effectiveness (non-inferiority) and QoL (superiority). Oncological effectiveness is defined as treatment failure, that is, pathologically proven clinically significant (meaning Gleason 7 or higher) recurrent disease and/or the medical indication for retreatment with salvage treatment (RP, RT or systemic treatment) in the focal therapy group, and as a biochemical recurrence (defined as at least two PSA values that are 0.2 ng/mL or higher in the RP group and according to the Phoenix criteria (increase in PSA of≥2 ng/mL above nadir) in the RT group) and/or salvage local or systemic treatment in the radical whole-gland treatment group. The primary endpoint for oncological effectiveness is set at 36 months of follow-up. QoL will be measured using the functional assessment of cancer therapy prostate cancer (FACT-P) overall score at 12 months. The FACT-P is a disease-specific questionnaire for PCa that evaluates an overall score to assess the QoL as well as per domain. The questionnaire contains five domains, including 27 questions in total and prostate-specific questions consisting of 12 questions. The domains will be assessed as secondary outcome measures.

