### Analysis

Descriptive statistics will be used to summarise the data. For the oncological effectiveness, a one-sided 95% upper confidence bound will be created for the percentage difference in pathologically proven recurrent disease and/or (indication for) re-treatment (salvage treatment). If this bound is less than the non-inferiority margin of 15%, focal therapy will be declared to be non-inferior to usual care, that is, RP/RT. For the QoL, outcome differences between the two groups will be calculated with 95% CIs. All data will be analysed according to the intention-to-treat principle, including all randomised participants in the groups to which they were originally assigned, regardless of protocol deviations or loss to follow-up. In addition, to test robustness of the results, per-protocol and as-treated analysis will be performed regarding oncological effectiveness and QoL.

Furthermore, for secondary QoL outcomes, individual item responses will be used to derive the proportion of men reporting a moderate or big problem (or equivalent).

Metastasis-free survival, disease progression, disease-specific mortality and all-cause mortality will be presented with Kaplan-Meier curves. Procedure time and hospital care stay will be summarised using descriptive statistics. Treatment-related complications will be recorded according to the Clavien-Dindo classification. An overall risk difference for the overall complication rate and a 95% CI, and a risk difference per complication and their corresponding 95% CIs will be calculated. Pathology results will be summarised using descriptive statistics.

Cost-effectiveness will be performed from a societal perspective as per Dutch guidelines for economic evaluation.^18^ Costs will be calculated according to the Dutch guideline for costing research. Average costs will be calculated in both groups and differences will be calculated inclusive of 95% CIs. Effectiveness will be measured in terms of quality-adjusted life years (QALYs). These will be based on the utility scores as measured with the EQ-5D-5L, using the area under the curve method. Incremental cost-effectiveness ratios will be calculated by dividing estimated differences in costs by differences in QALYs. Uncertainty will be addressed by means of non-parametric bootstrapping and, where relevant, one-way sensitivity analyses.

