We expect several challenges in executing our study. First, in previous studies no differences have been observed between the different focal therapies,^8 14^ but these techniques have not been directly compared within a single study. We aim to gain more insights into potential existing differences between the different modalities. For this aim, we will perform exploratory analyses for the focal therapies versus the radical treatments. Adjustment for centre will not be possible in these analyses since the type of focal therapy is centre-dependent; also the offered standard of care modalities differ between the centres. Furthermore, the different centres may have different perioperative protocols or complications.

Second, another complexity in this study is the difference in follow-up protocols between the treatment arms. In the standard of care arm, PSA is used as the primary follow-up marker. After RP the PSA level is expected to become undetectable within 2 months.^20^ PSA levels in RT drop more slowly compared with RP. No optimal cut-off value has been determined, but in current clinical practice a PSA<0.5 ng/mL is set as a favourable outcome after RT.^21^ However, after focal therapy, PSA monitoring becomes less reliable since the untreated part of the prostate continues to function and produce PSA as before. This necessitates a different follow-up approach for patients in the focal therapy arm. In this trial, we will perform MRI and biopsies as an additional part of the follow-up after focal therapy, as MRI has proven effective in detecting new or recurrent lesions in the prostate. Recently, scoring systems have been developed to evaluate post-focal treatment MRIs, in which the likelihood of recurrent disease is scored.^22 23^ These systems offer guidance on subsequent steps, ranging from continued observation to additional diagnostic procedures such as biopsies. We will implement such a scoring system (PI-FAB scoring system) alongside standardised biopsies at 1-year follow-up to confirm the presence or absence of a tumour after focal treatment. This approach allows us to validate the scoring system by comparing its outcomes with biopsy results.

Third, QoL will be assessed using patient-reported questionnaires, which may be subject to bias such as recall bias and response bias. These questionnaires are, however, validated, and the use of these questionnaires aims to reduce these biases.

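### The oncological co-primary endpoint is defined by group with unequal components, gives no matching criterion for men who do not get their assigned treatment, and is worded differently in the Analysis section

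*Protocol article*

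**What the plan says.** Under Primary endpoints, the protocol article gives each group its own failure rule at 36 months.

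- **Focal therapy:** pathology showing recurrence of Gleason 7 or higher, and/or "the medical indication for retreatment with salvage treatment (RP, RT or systemic treatment) in the focal therapy group".
- **Radical treatment:** biochemical recurrence, "defined as at least two PSA values that are 0.2 ng/mL or higher in the RP group and according to the Phoenix criteria" after RT, "and/or salvage local or systemic treatment in the radical whole-gland treatment group".

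Under Analysis, the non-inferiority comparison is described with a single wording, the "percentage difference in pathologically proven recurrent disease and/or (indication for) re-treatment (salvage treatment"). Biochemical recurrence does not appear there, and the bracketed term for indication is not limited to one arm.

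The same section analyses by intention to treat, "including all randomised participants in the groups to which they were originally assigned, regardless of protocol deviations or loss to follow-up". It adds per-protocol and as-treated analyses for both co-primary endpoints, and Kaplan-Meier curves for metastasis-free survival, disease progression, disease-specific mortality and all-cause mortality.

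The Discussion explains why the arms are followed differently: "after focal therapy, PSA monitoring becomes less reliable since the untreated part of the prostate continues to function".

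**The concern.** The PSA criteria depend on the treatment a man received, whereas the primary analysis groups men by the treatment they were assigned. The two agree only when everyone gets the assigned treatment. In an open comparison of organ-sparing with radical treatment, some men may not.

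The salvage component is also unequal. An indication is enough in the focal arm, while the radical arm names only the treatment. The Discussion's reason for not relying on PSA after focal therapy supports biopsy versus PSA. It does not support indication versus treatment given.

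A non-inferiority conclusion rests on one risk difference against a 15-point margin. If deviating men are scored by a rule that does not fit their treatment, that difference shifts for reasons unrelated to disease control. The two sections also disagree on whether biochemical recurrence is part of the endpoint, which for the radical arm is the main component.

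**Working it through.** **Who is scored how, on a literal reading of Primary endpoints under intention to treat**

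- Focal arm, receives RP or RT: no PSA criterion. A PSA relapse counts only if pathology proves recurrence or salvage is indicated.
- Radical arm, receives focal therapy or nothing: neither PSA rule names him, and biopsy-proven recurrence is not in the radical definition. He counts only if salvage treatment is given.
- Salvage indicated but not started: a failure in the focal arm, not by itself a failure in the radical arm.

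Under the Analysis wording, the third difference disappears, but PSA recurrence no longer counts for anyone.

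**Reproducing the plan's sample size**

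Inputs from Sample size: margin 15 points, expected difference 5 points, one-sided alpha 5%, power 80%, 356 men. The article gives no failure rates by arm. Assuming 15% radical and 20% focal:

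n per arm = (1.645 + 0.842)² × (0.15 × 0.85 + 0.20 × 0.80) / (0.15 − 0.05)² = 6.183 × 0.2875 / 0.01 = 177.8, so 178 per arm and 356 in total.

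This matches, but the rates are back-solved: 14% versus 19% gives 340 and 16% versus 21% gives 372.

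**Effect of mis-scored men**

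With pR and pF the observed radical and focal failure rates and 178 per arm:

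chance of declaring non-inferiority = Φ{[0.15 − (pF − pR)] / SE − 1.645}, SE = √{[pR(1 − pR) + pF(1 − pF)] / 178}.

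Type I error is taken at true rates of 15% and 30%, power at 15% and 20%. Deviating men are assumed to have the same underlying failure rate as the rest of their arm. The share deviating is also an assumption; the 5% in the article is drop-out.

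1. *Share of the focal arm scored as non-failures.* At 5% (about 9 men), pF = 0.30 × 0.95 = 0.285 and SE = 0.0431. Φ(0.015/0.0431 − 1.645) = Φ(−1.297) = 9.7%. At 2% the result is 6.6%, at 10% it is 17.3%. These are upper bounds, because an indication for salvage would still count for some of these men.
2. *Share of the radical arm that cannot fail.* At 5%, pR = 0.15 × 0.95 = 0.1425. Type I error: SE = 0.0432, Φ(−0.0075/0.0432 − 1.645) = Φ(−1.819) = 3.4%. Power: difference 0.0575, SE = 0.0398, Φ(0.0925/0.0398 − 1.645) = Φ(0.678) = 75%, against 80% with no deviation. These too are extremes, because salvage treatment would still count.
3. *Both at once, 5% in each arm.* pR = 0.1425, pF = 0.285, difference 0.1425, SE = 0.0428: 7.1%.

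**Range over the assumed radical rate** (178 per arm, 5% share, focal 15 points worse for type I error and 5 points worse for power)

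- Radical 10%: type I error 9.3% in case 1 and 3.8% in case 2; power in case 2 falls from 89% to 86%.
- Radical 20%: type I error 10.3% in case 1 and 3.1% in case 2; power in case 2 falls from 73% to 66%.

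**The case against.** Treatment-specific criteria are a reasoned choice, and the article lists unequal follow-up as a limitation. Per-protocol analysis would normally remove men who did not get their assigned treatment, and as-treated analysis regroups them, so both ease the scoring problem. A detailed SAP is promised before database lock and may add a scoring rule.

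Much of this stands. Different criteria alone are not the defect, and an SAP could settle the deviating men. But the unequal salvage wording and the conflict between the two sections are in the published text, and an SAP would have to choose between them. The per-protocol and as-treated analyses are supportive; they leave the primary analysis as it is and are not stated to use a common event.

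Three stronger readings are tempting and are not supported:

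- *That no analysis uses the same event in both arms.* Metastasis-free survival and mortality do. They are secondary and not tied to the margin.
- *That a radical-arm man who keeps his prostate fails automatically at 0.2 ng/mL.* With 5% such men, pR would be 0.15 × 0.95 + 0.05 = 0.1925 and type I error about 24% (57% with 10%). The article applies that threshold only after RP, so these figures rest on a rule it does not contain.
- *That deviating men cannot be scored at all.* The salvage components still apply to many of them. What is missing is a criterion that fits the treatment they had.

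**Conclusion.** The point holds in limited form. The oncological co-primary endpoint has unequal salvage components, has PSA rules that do not reach every man in the intention-to-treat groups, and is worded in two conflicting ways. No common-event analysis is stated for it.

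The bias has no fixed direction. Focal-arm deviation pushes towards non-inferiority (type I error up to about 10% at a 5% share). Radical-arm deviation on a literal reading pushes against it (about 3.4%, with power near 75%). Counting an indication only in the focal arm can only add focal failures, so that asymmetry also works against non-inferiority. All these sizes depend on assumed failure rates and deviation shares, and would be negligible if almost everyone receives the assigned treatment. This is an inexpensive improvement to make, not a flaw that invalidates the design.

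**What to change.** 1. Reconcile Primary endpoints with Analysis so that one definition stands, stating explicitly whether biochemical recurrence is included.
2. Keep the intention-to-treat grouping, but apply the failure criterion that matches the treatment received: the relevant PSA rule after RP or RT, the biopsy rule after focal therapy. State what counts for a man who receives none of these.
3. Use the same salvage wording in both arms: indication for, or start of, salvage treatment.
4. Pre-specify a supportive 36-month risk difference on one arm-neutral event: start of salvage whole-gland or systemic treatment, metastasis, or prostate cancer death.

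The cost is revised wording and one extra analysis, mainly on data already planned. The 36-month results are expected at the end of 2029, so there is time to do this before outcomes are known. There are two drawbacks. The common event is rarer and later, so it can only be supportive. Scoring by treatment received also makes the criterion depend on what happens after randomisation, although the comparison groups stay as randomised.
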